**Secondary outcome measures**

Secondary outcomes include:

1. Physical health of participants measured using % of participants with good health, % of participants with a chronic illness other than Hepatitis B, the average number of chronic illnesses, % of participants who were sick in the last 30 days, % who sought treatment from a qualified health worker if sick in the last 30 days, % of participants with abnormal levels of Gardnerella vaginalis (GV), Mobiluncus, Candida and streptococcal in the vagina (only at endline)

2. Physical health of economic dependents measured using % of economic dependents with good health, % of economic dependents with a chronic illness, the average number of chronic illnesses per economic dependent, % economic dependents who were sick in the last 30 days, % economic dependent who were sick during sex act with last client, % economic dependents who were sick during sex act with the penultimate client, % of children with good health

3. Beliefs regarding control over own health measured using % who believe that nothing can be done to prevent illness, % who believe that being in good health is a matter of luck

4. Poverty measured using total expenditures, asset index, income from sex work, amount of savings, % who have Informal shock-coping strategies, average amount of transfers received and sent, % who have a debt, amount of the debt, food insecurity

5. Education/training measured using % school dropout, new enrolment in schools, % who are undertaking professional training

6. Other occupation measured using transitions out of sex work, % who have other occupation, share of sex work income in total income

7. Risky sexual behaviours measured using % of condom use with last and penultimate client using a double list experiment and the colourbox method, a newly indirect elicitation method developed by the team members, number of clients per week, type of sex acts performed with last client, self-reported risk preferences with sex (out of 10 scale), % of were pregnant the last 6 months, % who performed both transactional sex and sex work

8. Violence measured using % who experienced violence (threats, physical, sexual, emotional/psychological) the last time they had sex with a client, % who experienced violence the penultimate time they had sex with a client, % who experienced violence by a current partner in the last 6 months, % who experienced violence by a sugar daddy in the last 6 months, % who experienced violence by another sex worker in the last 6 months, % who experienced violence by an occasional client in the last 6 months, % who experienced violence by a regular client in the last 6 months, % who experienced violence by police in the last 6 months, % who experienced violence by their pimp in the last 6 months, % who experienced violence by hostel owners in the last 12 months

9. Stress measured using perceived stress scale 4 (PSS-4)

10. Self-efficacy measured by participants' ability to deal with issues in different domains of their life

11. Loneliness measured using UCLA 3 Item Loneliness scale

12. Discrimination measured using Everyday Discrimination Scale (Short Version)

13. Stigma measured using % who have at least one of their family or friends aware that the participant has having paid sex, % who expect discrimination by family if HIV positive, % who consider themselves as a sex worker

14. HIV and STI knowledge measured using knowledge of participants regarding ways HIV can be transmitted, average knowledge of STI symptoms

15. Social networks measured using the number of friends in sex work, the number of peers who provide financial support

16. Mental health measured using % that are depressed using PHQ-9 scale, % who are happy, % satisfied with life, % with good self-esteem

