**Intervention description {11a}**

The insurance product, provided by GMC Insurance, covers the participant and up to six of their (nominated) economic dependents and is offered for 12 months. An economic dependent is anyone that depends on the participant financially for health care and can include family members, friends and sex work intermediaries (e.g., pimp). The health insurance product provides free health coverage, there are no out-of-pocket costs, with a cumulative ceiling for each group (the participant and their economic dependents) of 500 000 FCFA (= 638,55 GBP, in 2022 prices) following an illness or an accident and is only valid at the Cité Verte Hospital, Yaoundé, Cameroon. The negotiated ceiling of 500 000 FCFA provides good coverage of health expenses for 12 months in Cameroon. If the sum of 500,000 FCFA has been reached (by the participant and their economic dependents combined), participants must pay for the health expenses themselves. Before the group reaches the 500 000 FCFA limit, the participant will be notified to ensure that they are informed when consuming health care. Costs covered by the insurance product are: consultation fees; pharmaceutical fees; medical fees and; hospitalization fees for non-chronic pathologies. Costs not covered by the insurance product are: chronic diseases (e.g. diabetes, high blood pressure, asthma, sickle cell anaemia, obesity...); maternal health care (prenatal care, delivery, postnatal care); illness resulting from civil or foreign war, civil commotion or riot; injury following a violent quarrel except in cases of self-defence; epidemics declared as such by a competent authority (e.g. COVID-19); cosmetic care; dietary care; weight loss or rejuvenation; sterility or abortion treatment; psychiatric treatment; alcoholism; dialysis; dental care and; ophthalmologic care.

The insurance product was rolled out on the 15^th^ of November 2021 and ended on the 14^th^ of November 2022.

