**Strategies to improve adherence to interventions {11c}**

The main strategies employed to encourage participant adherence to the intervention is to ensure that participants and their economic dependents have the best possible experience whilst accessing care at the hospital and to reduce the barriers to access to care. A key concern is that participants or their nominated economic dependents will not go to the hospital to seek care when sick because they face large barriers to access e.g., lack of understanding of illness, distrust in healthcare or not having enough money to get to the hospital. Treatment participants receive information at randomisation, midline and endline regarding what is provided as part of the health insurance product, how to access it and whom to contact if they are having difficulties. Data is collected during the midline and endline survey regarding the participant's experience of using the health insurance product. If the participant has not used the insurance product because they forgot they are part of the treatment group the participant is reminded of the health insurance product and encouraged to use the intervention if needed by the enumerator and the site supervisor at the end of the survey. If the participant has had a bad experience whilst accessing care at the hospital, this is reported to the site supervisor and to the research staff. This problem will be discussed whilst the participant is being surveyed by the enumerator. At the end of the survey, the site supervisor will discuss their experience with the participant and ensure that any issues will be resolved and encourage them to use their health insurance product if needed. Experienced POWER enumerators are based at the hospital throughout the intervention period to support the patients throughout their clinical pathway. If there are any issues with treatment or access to care, the POWER staff report it directly to the research team for a resolution. The CBOs and specifically peer leaders and mobilisers support the adherence of participants to the intervention by keeping in regular contact with the participants throughout the lifetime of the project. Regular contact allows participants with concerns regarding the project or the intervention specifically the opportunity to speak up. Any problems are communicated to the research team and resolved. All resolutions are discussed with the participants. Peer leaders and mobilisers use their strong relationships with the participants and their status in this vulnerable population to engage participants and encourage adherence to the intervention.

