**Assignment of interventions: Blinding**

**Who will be blinded {17a}**

Participants and care providers will not be blinded. Researchers will not be blinded during the conduct of the study to support the smooth-running implementation of the intervention. However, data analysts will be blinded during the data analysis period.

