**Data collection and management**

**Plans for assessment and collection of outcomes {18a}**

There are several methods of data collection. The socio-economic and biobehavioural surveys occur over three time periods: baseline, 6 months after baseline (midline), and 12 months after baseline (endline). The surveys are administered in both French and English, depending on the participant's language preference. The primary outcomes of the study are STI acquisition and HIV status will be measured via the biobehavioural and socioeconomic survey conducted at baseline, midline and endline. At baseline, we will test for syphilis, chlamydia, gonorrhoea and trichomoniasis. For financial reasons, we will only collect HIV and the two most prevalent STIs at the midline. At endline we will test for all the STIs tested at baseline (syphilis, chlamydia, gonorrhoea and trichomoniasis). In addition, to allow for a better understanding of the participants' non-sexually transmitted infections status, the levels of GV, Mobiluncus, Candida and streptococcal in the vagina will also be tested. Testing the levels of these bacteria and fungi is a secondary outcome. It is important as sexual activity is associated with an increased risk of imbalance of these bacteria or fungi in the vagina which may lead to infections such as Bacterial vaginosis (BV), Candidiasis and Group B Strep infection. Evidence suggests that there is a positive relationship between a person having these infections and an STI and HIV(17). Biological tests (blood tests and vaginal swabs) to test for STIs, HIV and non-sexually transmitted bacteria and fungi are conducted at the same time as the socioeconomic survey.

Other secondary outcomes are measured via the biobehavioural and socioeconomic survey conducted at baseline, midline and endline. Additional measures for secondary outcomes will also be captured in the fortnightly SMS survey. The survey questionnaire will include sociodemographic questions, income, health status, demand for healthcare, economic shocks, STI prevention, risky sexual behaviours, violence, personality traits and preferences.

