**Statistical methods**

**Statistical methods for primary and secondary outcomes {20a}**

All statistical analyses will be conducted using STATA. Descriptive statistics will first be used to summarise participant characteristics between the study groups. To investigate the effect of health insurance on primary and secondary outcomes, the analysis will use an intention-to-treat (ITT) approach where participants will be analysed in their allocated randomised study group. If there are non-compliers, i.e., participants and economic dependents who do not use the health insurance product when sick, we will also estimate the local average treatment effect (LATE). To investigate the effect of health insurance on primary and secondary outcomes, baseline characteristics will be compared for the treatment and control groups and determine whether there is differential attrition between the two groups. Outcomes for the treatment versus the control group will then be compared accounting for any baseline or attrition differences using ordinary least squared. The analysis will be conducted for all women and then separately for women engaging in transactional and commercial sex separately. A causal mediation analysis will be conducted to assess how much of the effect of health insurance on STI and HIV acquisition operates through risky sexual behaviours.

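### Care-seeking is measured only among women who report being sick after randomisation, so its arm comparison loses the protection of randomisation if insurance changes who is sick or who reports it

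*Protocol*

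**What the plan says.** Under Secondary outcome measures, item 1 (physical health of participants), the Protocol lists the percentage "who sought treatment from a qualified health worker if sick in the last 30 days". Immediately before it, the same item lists the percentage "of participants who were sick in the last 30 days". Section {18a} gives the timing: "Other secondary outcomes are measured via the biobehavioural and socioeconomic survey conducted at baseline, midline and endline". Midline and endline fall after randomisation, and section {17a} states: "Participants and care providers will not be blinded".

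On analysis, section {20a} says "the analysis will use an intention-to-treat (ITT) approach where participants will be analysed in their allocated randomised study group", with outcomes compared "accounting for any baseline or attrition differences using ordinary least squared". Sections {20a} and {20c} add a local average treatment effect for non-compliance. Nothing addresses selection into the group of women who were sick.

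Health care utilisation appears separately among the indicators of implementation, without a definition or denominator.

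**The concern.** Randomisation makes the arms comparable as wholes. It does not make subsets comparable when they are chosen by something that happens after allocation and that allocation may influence. Being sick in the last 30 days is such a thing at midline and endline, and the Protocol treats it as a possible effect of insurance by listing it as an outcome.

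There are plausible routes in both directions. Section {11a} says: "Costs covered by the insurance product are: consultation fees; pharmaceutical fees; medical fees", and also hospital fees for non-chronic conditions. Free care could prevent or shorten illness. It could also lead women to recognise and report minor illness they would otherwise ignore: section {11c} names poor understanding of illness as a barrier and gives treated women information and reminders.

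Keeping each woman in her allocated arm does not restore comparability within the sick subset. Adjusting for baseline and attrition differences does not guarantee it either, and the local average treatment effect deals with a different problem. The Discussion warns that under-use of care could prevent evaluation of the intervention, so a misleading care-seeking figure would affect how the trial's results are read.

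**Working it through.** The Protocol gives no illness rate, care-seeking rate or effect size for this outcome, so there is no figure of its own to reproduce. All rates below are assumptions chosen to show the mechanism.

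**Case 1: insurance adds reported minor illness.** Let *s* be the share of controls sick, *c* their care-seeking rate, *e* the extra share of insured women reporting illness, *m* the care-seeking rate of those extra women, and *d* the true gain among the already-sick.

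- Conditional rate, control: *c*
- Conditional rate, treatment: [*s*(*c* + *d*) + *e·m*] / (*s* + *e*)
- Sick and sought care, over all women: *s·c* in control; *s*(*c* + *d*) + *e·m* in treatment
- Gain at which the conditional contrast is zero: *d* = *e*(*c* − *m*) / *s*

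Take *s* = 30%, *c* = 60% and *d* = 0. Control: conditional rate 60%; over all women 0.30 × 0.60 = 18%. Treatment with *e* = 10%:

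- *m* = 20%: (0.18 + 0.02) / 0.40 = 50%; over all women 20%
- *m* = 30%: (0.18 + 0.03) / 0.40 = 52.5%; over all women 21%

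The conditional outcome falls by 7.5 to 10 points while care-seeking over all women rises by 2 to 3 points. Across a range of *e*, with *m* = 20% to 30%:

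| Extra illness | Conditional rate, treatment (control 60%) | All women, treatment (control 18%) | Gain giving a zero contrast |
|---|---|---|---|
| 5% | 54.3%–55.7% | 19%–19.5% | 5–6.7 points |
| 10% | 50%–52.5% | 20%–21% | 10–13.3 points |
| 15% | 46.7%–50% | 21%–22.5% | 15–20 points |

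A gain above the last column makes the contrast positive, but still too small. With *e* = 10%, *m* = 20% and *d* = 20 points, the treatment rate is (0.30 × 0.80 + 0.02) / 0.40 = 65%, an apparent gain of 5 points against a true 20.

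**Case 2: insurance prevents illness.** Let *x* be the share of control-arm illness prevented, and *g* the amount by which the prevented cases would have sought care more often than the women who are sick in either arm. The conditional contrast is *d* − *x·g*.

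- Severe illness prevented: control has 10% severe (80% seek care) and 30% mild (40% seek care), so (0.08 + 0.12) / 0.40 = 50%. Insurance prevents the severe cases and raises care-seeking among the rest by 5 points, to 45%. Contrast: −5 points. Check: *x* = 25%, *g* = 40 points, 5 − 10 = −5.
- Mild illness prevented: control has 10% mild (20% seek care) and 30% other (60% seek care), so (0.02 + 0.18) / 0.40 = 50%. Insurance prevents the mild cases and changes nothing else, giving 60%. Contrast: +10 points with no true effect.

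For *x* from 5% to 30% and *g* from 10 to 40 points, the bias −*x·g* runs from −0.5 to −12 points. When *g* is negative the sign turns round, so the direction cannot be known in advance.

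**The case against.** Much of the case on the other side stands.

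- **Insurance may not change sickness at all.** That it does is a hypothesis. If neither illness nor its reporting changed, the conditional contrast would be unbiased. A reader might infer that insurance certainly alters who is sick; the documents only list sickness as an outcome, which leaves the question open.
- **The reversal is not inevitable.** Case 1 sets the true effect among the already-sick to zero, although free care is meant to raise it. A gain above about 5–7 points (with 5% extra illness) or 10–13 points (with 10%) removes the reversal, though not the bias.
- **This is not the only evidence on delivery.** A reader might take this item as the main proof that the intervention worked. The Protocol has a separate list of implementation indicators, asks about use of the product in the midline and endline surveys, and identifies insured patients at a dedicated hospital reception. However, its health care utilisation indicator is undefined.
- **The information is recoverable.** Multiplying the two planned percentages gives the share sick and seeking care (40% × 50% = 20% against 30% × 60% = 18%). That works for crude figures, but the adjusted contrast that would be tested and reported is still the conditional one.
- **The conditional question is natural.** Section {11c} worries that people "will not go to the hospital to seek care when sick". This justifies showing the percentage, but not reading its arm difference as a randomised effect.
- **A single unconditional percentage can also mislead.** In the severe-illness example, sick and sought care falls from 20% to 0.30 × 0.45 = 13.5% because illness was prevented. This is correct and shapes the fix.

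**Conclusion.** The point holds in a limited form. The outcome definition itself fixes a post-randomisation denominator, so this is not a detail left to an analysis plan. If insurance changes illness or its reporting, the contrast among the sick is not a randomised comparison, and the planned analysis does not repair it.

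Under the assumed rates the distortion runs from under 1 point to more than 10, in either direction. These figures show what is possible; they are not a forecast, because the Protocol supplies none of the inputs.

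The consequence is small: one component of one of 16 secondary outcomes. Nothing here bears on the STI or HIV comparisons.

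**What to change.** At each follow-up survey, classify every randomised woman as not sick, sick and sought qualified care, or sick without qualified care, all over the last 30 days. Compare the arms on the three categories together, with the same handling of missing surveys as for other outcomes. The planned OLS can be kept, one indicator per category: with the same women and covariates, the three arm differences sum to zero, so a shift from one category shows up in the others. Keep the percentage among the sick, labelled descriptive. It would help to give health care utilisation a definition and denominator at the same time.

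The cost is minor recoding of answers already planned for collection, plus a documented late change to a secondary outcome definition. Insurance ended on 14 November 2022, the Protocol is the final version of 10 March 2023, and amendments go to two ethics committees. Researchers are unblinded during conduct but analysts are to be blinded, so the change should be dated and recorded before anyone examines this outcome by arm.

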Recent studies have shown that women mainly adopt risky sexual behaviours to cope with negative income shocks (e.g., agricultural and climatic shocks, illness or death of family members) and suggest that economic shocks are a substantial piece of the HIV puzzle in Africa (3). Researchers have previously explored the link between poverty and HIV through cash transfers targeting adolescent girls and young women (4). Cash transfers can be an effective way to reduce risky sexual practices among women by increasing their income. However, evidence regarding their effectiveness to prevent HIV is mixed. In Malawi, cash transfers were found to reduce HIV prevalence by 64% (5) while they had limited effect in Kenya (6) and no effect in South Africa (7). The POWER project is based on the assumption that income variability matters more than income level for HIV acquisition, which could explain why cash transfer programs are not always effective. While the literature shows mixed evidence regarding the effect of poverty on HIV prevalence among women (8), there is robust evidence demonstrating that women adopt risky sexual behaviours as a way to cope with economic shocks. Economic shocks are defined as any events that lead to a sudden increase in expenditure level (e.g., illness, COVID-19) or a decrease in income level. In Kenya, it was estimated that an illness of a family member led sex workers to increase unprotected sex by 21 per cent (9). Another study found that each time a village in Africa suffered from a drought, it led to an increase in HIV prevalence in that village by 11 per cent (10). Hence, there is a need to explore whether the effectiveness of some cash transfer programs in reducing HIV acquisition is due to their role in protecting against economic shocks. If so, cash transfers may fail to prevent HIV infection if the amount offered is not large enough to protect against economic shocks or if they are received outside a shock period.

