There are several reasons why economic shocks may lead to STIs and HIV acquisition. The main reason lies in the fact that the low access to formal well-paid jobs and productive assets makes women in Africa prone to use commercial and transactional sex as risk-coping strategies. Such strategies may be attractive given that they allow women to raise money quickly and they can earn up to three times more compared to other occupations (11). Relationships developed with men through commercial and transactional sex can also result in other financial or in-kind gifts, which could also help women to cope with economic shocks (12). Women who engage in commercial and transactional sex are incentivised to provide unprotected sex because men are generally willing to pay more for unprotected sex. It is estimated that sex workers can earn 9% more in Kenya and 66% more in India (11) for an unprotected sex act. In addition to unprotected sex, commercial and transactional sex are risky practices because they often lead to multiple, concurrent sexual partners and partners at greater risk of HIV infection (older men and sex workers’ clients). In addition to increasing risky behaviours, economic shocks may also lead to STI and HIV infection if households cut health expenditures concerning STI treatment and HIV prevention services.

Determining whether an economic shock is the missing piece of the HIV puzzle is critical as economic shocks are very common in Africa and these women often lack risk-coping strategies. Economic shocks are a key issue for many African households. At least 60% of African households report large and sudden losses in income every year (13) but only 10% of the poorest households in Africa benefit from social safety net programs to negate income fluctuations (14). Among the shocks experienced by households, health shocks are of particular concern given that they are more frequent, more costly and more concentrated among the poor than other economic shocks (15). If women adopt risky sexual behaviours to cope with negative economic shocks providing women with formal risk-coping strategies could be a very promising approach to preventing HIV. However, no previous study has been designed to specifically answer this research question. Hence, there remain important gaps in understanding.

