**Objectives {7}**

**Research Hypothesis**

The main research hypothesis is that women who engage in transactional and commercial sex in Africa use risky sex as a way to cope with economic shocks. Providing health insurance for themselves and their economic dependents is effective to reduce risky sexual behaviours and in turn, prevent STIs and HIV infection among women and girls who engage in commercial and transactional sex.

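### Two indicators of dependents' health are read at the woman's client acts, so a change in when she takes clients can move them without any change in health

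*Protocol*

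**What the plan says.** In Outcomes {12}, Secondary outcome measures, item 2 opens with "Physical health of economic dependents measured using % of economic dependents with good health" and lists seven indicators. Two are tied to the participant's sex acts: "economic dependent who were sick during sex act with last client" and "economic dependents who were sick during sex act with the penultimate client". The other five (good health, chronic illness, number of chronic illnesses, sickness in the past month, children's health) are not. One of those five is the share of "economic dependents who were sick in the last 30 days".

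The Research Hypothesis says that "women who engage in transactional and commercial sex in Africa use risky sex as a way to cope with economic shocks", and that "Providing health insurance for themselves and their economic dependents is effective to reduce risky sexual behaviours". Background and rationale {6a} goes a step further: poor access to well-paid work "makes women in Africa prone to use commercial and transactional sex as risk-coping strategies", and such sex is described as a quick source of money. The only size given for a response to family illness is that "an illness of a family member led sex workers to increase unprotected sex by 21 per cent".

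Statistical methods {20a} compares primary and secondary outcomes between arms by least squares, adjusting for baseline or attrition differences. Nowhere does the protocol mark the two act-based indicators as measures of mechanism.

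**The concern.** A health indicator should sample illness at times that the intervention cannot shift. A calendar window does so. The time of a client act does not, if illness prompts the act and insurance weakens the prompt. Uninsured women's acts would then fall disproportionately on days when a dependent is sick and insured women's acts would not, so the insured arm would show a lower percentage with the same days of illness. Adjustment for baseline or attrition differences does not remove a shift in timing that arises after randomisation.

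What is at stake is interpretation. A behavioural effect, which the trial wants to detect, could be reported as better health of dependents. The sign is not assured either: if uninsured women take fewer clients while nursing a sick dependent, and insurance removes that, the insured arm would appear to have sicker dependents.

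**Working it through.** The protocol states no figure for these indicators, so there is nothing to reproduce. The check asks how far they can move when dependents' illness is identical in both arms.

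**From the protocol.** 568 control and 579 insured women, 5% significance (Sample size {14}). Two-sided testing is assumed, since sidedness is not stated.

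**Assumed, because the protocol gives no value.**
- A dependent is sick on a share s of days, 10-30%, in both arms.
- Sick spells last 7 days on average.
- There is one value per woman.
- Uninsured women take clients at rate w per week on well days and k·w on sick days.
- Insurance removes the response completely (k = 1).
- k is set at 1.21 and 1.5. The 1.21 borrows the 21% quoted from the background, which concerns unprotected sex and not the timing or number of acts, so it is illustrative only. The 1.5 has no source.

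**Formulas.** Sickness is a two-state process and acts are Poisson with a rate that depends on the state. With 7-day spells, time in weeks and b = s/(1−s):
- Last act before the survey: p1 = k(s·w + b) / (k·w + 1 + k·b).
- Penultimate act: p2 = k(p1·w + b) / (k·w + 1 + k·b).
- Randomly chosen act: s·k / (s·k + 1 − s).

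As w approaches 0, p1 tends to the random-act value. As w grows, p1 tends to s, because the last act then nearly samples the survey day.

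**Example.** s = 0.20 gives b = 0.25. With k = 1.21 and w = 1, p1 = 1.21 × 0.45 / (1.21 + 1 + 0.3025) = 0.5445/2.5125 = 21.7%, and p2 = 1.21 × (0.2167 + 0.25)/2.5125 = 22.5%. The insured arm reads 20.0%. For p1 the standard error is √(0.2167×0.7833/568 + 0.20×0.80/579) = 0.0240, so the difference of 0.0167 is 0.70 standard errors and is significant in about 11% of trials. A simulation of another case (s = 20%, k = 2, w = 1) gave 25.9% against 25.7% by formula.

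**Control-arm reading at s = 20% (insured arm 20.0%), and chance of a false significant difference over s = 10-30%.**

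| k | Clients/week | Last act | False significance | Penultimate act | False significance |
|---|---|---|---|---|---|
| 1.21 | 1 | 21.7% | 8-14% | 22.5% | 12-23% |
| 1.21 | 7 | 20.4% | 5-6% | 20.8% | 6-7% |
| 1.5 | 1 | 23.5% | 17-41% | 25.3% | 34-72% |
| 1.5 | 7 | 20.8% | 6-7% | 21.6% | 7-13% |

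For a randomly chosen act at s = 20%, the reading would be 23.2% (k = 1.21) or 27.3% (k = 1.5). Over s = 10-30% the false-significance rates would be 17-33% and 60-90%.

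**After the fix.** For a window not tied to acts, such as the 30-day item, the expected value depends on illness alone whatever k is. The arm difference from timing is then 0.

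**The case against.** The strongest reply is that the hypothesis does not require the effect. It speaks of risky sex, and insurance could work through condom use alone, leaving act timing and these indicators unchanged. That stands. A reader might infer that the trial's own hypothesis makes the indicators move; the documents do not support so strong a reading. The timing channel comes from the background section and is plausible, not entailed.

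Second, a reader might take the random-act rates (17-33% and 60-90%) as the size of the problem. The surveys are scheduled by calendar and the items concern the last two acts, so those rates are upper limits, approached only when clients are infrequent. Complete removal of the response is also a favourable case: the insurance excludes chronic disease and has a ceiling, and the Discussion warns of under-utilisation.

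Third, the consequence is limited. These are two of seven indicators in one of 16 secondary domains. Nothing in the protocol makes them confirmatory or ties a decision to them, and disagreement with the 30-day item would be a warning. That also stands, and it sets the severity. It does not justify the heading: with no timing response the two items add little to the 30-day item, and with one they mix behaviour and health.

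**Conclusion.** The concern holds in conditional form. The two indicators can differ between arms through the timing of client acts alone, so they are not clean measures of dependents' health. Whether they do differ depends on a timing response that the background suggests and the hypothesis does not strictly need.

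The size is unknown. Under the stated assumptions it runs from negligible, when clients are frequent relative to illness spells, to material, when clients are few and the response is strong; it is larger for the penultimate act than for the last. If insurance also truly improves dependents' health, the two effects cannot be separated in these items. Women who leave sex work add a further selection, since their last act is older or absent from follow-up.

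Severity is minor. The other five indicators in item 2, the primary outcomes and the sample size are unaffected.

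**What to change.** Take both indicators out of item 2. List them under item 7 (risky sexual behaviours) or with the shock analyses in {20b}, defined as the share of recent client acts that took place while a dependent was sick and interpreted as coping behaviour. Keep the 30-day item as the sickness measure for dependents' health.

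The cost is wording in the outcome list. The same questions are asked and the same data are used. The dependents' health domain loses two of its seven indicators, and the trial gains a more direct measure of its proposed mechanism. As follow-up is already under way, the reclassification should be dated and recorded as an amendment.
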